### Harms

Although adverse events causally related to cognitive-behavioral rehabilitation are not expected, we will assess disability pensions and premature termination of rehabilitation in both groups.

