### Interventions

#### Cognitive-behavioral rehabilitation

The cognitive-behavioral rehabilitation program was developed for cardiac rehabilitation patients with mild or moderate mental illness or stress or exhaustion. The program complements standard cardiac rehabilitation with additional psychological and exercise interventions and follows the framework of cognitive-behavioral rehabilitation formulated by the German Pension Insurance [20].

Cognitive-behavioral rehabilitation is conducted as a group program, i.e., 8–12 patients who begin the rehabilitation program at the same time complete five specific additional cognitive-behavioral components together. Table 1 summarizes these five components, e.g., a psychological group, individual psychological sessions, relaxation training, a seminar on heart and psyche, and an exercise group. Moreover, Additional file 2 provides a detailed description of the five components according to the Template for Intervention Description and Replication [21]. The treatments beyond these five components follow – as in the control group – the recommendations for the rehabilitation of coronary heart disease published by the German Pension Insurance [18]. Cognitive-behavioral rehabilitation lasts for four weeks.

A detailed description of the psychological group can be found in Benninghoven et al. [14]. This group includes seven 90-minute sessions and is based on acceptance and commitment therapy [14, 22, 23]. It combines cognitive-behavioral therapy techniques with mindfulness- and acceptance-based methods and emotion-regulating strategies. In addition to complementary psychological and educational interventions, cognitive-behavioral rehabilitation is characterized by intensified exercise therapy, as there is strong evidence that exercise therapy reduces cardiovascular mortality and hospitalizations and improves quality of life [24].

**Table 1 Tab1:** Components of the cognitive-behavioral rehabilitation program

Brief name	Psychological group	Individual psychological sessions	Relaxation training	Seminar: Heart and psyche	Exercise group

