When and how much	During the rehabilitation program, seven sessions of 90 min each, in total 630 min	During the rehabilitation program, at least one 60-minute session	During the rehabilitation program, one session of 60 min and eight sessions of 30 min each, in total 300 min	During the rehabilitation program, two sessions of 60 min each, in total 120 min	During the rehabilitation program, individual admission assessment: one sessions of 30 min, cardiovascular exercise therapy: 20 sessions of 30 min each, ergometer training: one session of 60 min and 11 sessions of 30 min each, strength training: 6 sessions of 60 min each, coordination training: 10 sessions of 30 min each, in total 1680 min

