#### Standard cardiac rehabilitation

Controls receive the standard cardiac rehabilitation program in accordance with the recommendations for the rehabilitation of coronary heart disease [18]. To ensure that any potential benefits of the cognitive-behavioral rehabilitation program are not due to a longer rehabilitation duration of the cognitive-behavioral program, the standard rehabilitation program is also conducted for four weeks instead of the usual three weeks.

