##### Health-related costs

For our health economic evaluation, we use the Questionnaire for Health-Related Resource Use in an Elderly Population [40]. The questionnaire assesses, among others, the type of health insurance, medications taken in the last seven days, outpatient physician visits and therapeutic services used in the last 3 months, as well as rehabilitation measures, outpatient surgery and treatments in outpatient or inpatient hospitals in the last 12 months. The health-related costs are calculated using the rates proposed by Bock et al. [41].

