### Confidentiality

Participants are added to a password-protected study list (Microsoft Excel) with their name, address, and social security number upon consent to participate and are assigned an identification number. This list also documents the treatment group, consent, and the planned start of rehabilitation after randomization. This study list remains at the recruiting rehabilitation center. The rehabilitation center transmits a pseudonymized copy of this list exclusively with the pseudonym, treatment group, date of receipt of consent and planned start of rehabilitation electronically and encrypted to the University of Lübeck at the beginning of each week. The study list will be shredded by the rehabilitation center after all follow-up questionnaires have been sent out. As of that point, the data will be completely anonymized.

The rehabilitation center documents in another list (Microsoft Excel), in which participants are recognized only by their identification number (pseudonymized list), their date of birth, gender, the actual start of rehabilitation and the end of rehabilitation (if necessary, also the early termination of rehabilitation), selected clinical data collected in the rehabilitation center (systolic and diastolic blood pressure, ergometer performance in watts/kg, capacity for last job and other job, recommendations for subsequent services, diagnoses), and the therapeutic services performed during rehabilitation.

The participants’ questionnaires are provided with the identification number in the rehabilitation center and handed over to the study participants by a member of the research team for completion at the beginning and end of the rehabilitation. The participants deliver the questionnaires in an envelope at the reception of the rehabilitation center. Thereafter, these questionnaires are personally handed over to MB by DB every two weeks. The questionnaires of the follow-up assessments after 3 and 12 months, also tagged with the identification number, as well as the reminders, are sent from the rehabilitation center. A stamped return envelope addressed to the University of Lübeck is enclosed with this letter.

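### The harm comparison counts premature terminations without a reason, so it cannot separate medical events from personal departures and does not capture acute hospital transfers during the four-week stay

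*Protocol article*

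**What the plan says.** The Harms section begins "Although adverse events causally related to cognitive-behavioral rehabilitation are not expected" and then fixes what is looked at: "we will assess disability pensions and premature termination of rehabilitation in both groups". It names no cause of termination and no recording of acute events during the stay.

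The Confidentiality section itemises the centre's pseudonymized list. It holds the actual start and end of rehabilitation, "if necessary, also the early termination of rehabilitation", selected clinical data, diagnoses and the services delivered. A reason for early termination is not among the items.

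Other relevant statements:
- **Exercise.** The intervention section states that "cognitive-behavioral rehabilitation is characterized by intensified exercise therapy". Table 1 ends the exercise component with "coordination training: 10 sessions of 30 min each, in total 1680 min".
- **Duration.** "Cognitive-behavioral rehabilitation lasts for four weeks", and for controls "the standard rehabilitation program is also conducted for four weeks instead of the usual three weeks".
- **Hospital use.** Under Health-related costs, the questionnaire asks about "rehabilitation measures, outpatient surgery and treatments in outpatient or inpatient hospitals in the last 12 months". Table 2 schedules it at T3 only.
- **Oversight.** Participants and providers are not blinded (Blinding), and there is no external data monitoring committee (Data monitoring).

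**The concern.** The patients have cardiovascular disease, and one feature of the tested program is more intensive exercise. The harms of most interest are acute: a cardiac event, a transfer to hospital or a death during the four weeks. Neither planned measure identifies these. A disability pension is a distant social outcome. Premature termination includes acute events that end the stay, but mixes them with departures for family, work or personal reasons.

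The article aims to inform pension insurers whether the program could be recommended across Germany. If the report says that premature terminations were similar in the two arms, readers may take that as reassurance about safety. A count without causes cannot carry that meaning.

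**Working it through.** **1. What each planned source can show about the stay**

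| Source | When | Shows an acute medical event during the stay? |
|---|---|---|
| Premature termination (Harms; Confidentiality list) | During the stay | Only mixed with non-medical departures; a transfer that does not end the stay is not counted |
| Disability pension (Table 2) | T0, T2, T3 | No |
| Discharge diagnoses (Table 2) | T1 | Possibly, but not designated as harms and not linked to termination |
| Hospital item of the resource-use questionnaire | T3 | Essentially no (step 2) |

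**2. Window of the hospital item.** T3 is 12 months after the end of rehabilitation and the look-back is 12 months, so the window opens at 12 − 12 = 0 months, that is, at about discharge. Late returns after the reminders move it later. The four-week stay lies before it.

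**3. Exercise total.** Table 1 gives 30 + 20×30 + 60 + 11×30 + 6×60 + 10×30 = 30 + 600 + 60 + 330 + 360 + 300 = 1,680 min, as stated. This is the intervention arm's total. The controls' exercise is not quantified, so the excess cannot be derived.

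**4. What mixing does.** Let m be the medical termination rate and q the non-medical rate, with subscripts C (control) and I (intervention). The observed difference is

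(m_I − m_C) + (q_I − q_C).

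The documents give none of these rates and no figure for harms. All rates below are assumptions. The arm size is 410/2 = 205 (Sample size section).

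**5. Equal non-medical departures (q_I = q_C = q).** The absolute difference survives, but the ratio shrinks and the noise grows. Power for a two-sided 5% test of two proportions is Φ[(d − 1.96·se0)/se1], where se0 uses the pooled rate and se1 the separate rates.

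With m_C = 2%, m_I = 8%, q = 0:
- se0 = √(0.05×0.95×2/205) = 0.02153
- se1 = √[(0.02×0.98 + 0.08×0.92)/205] = 0.02132
- (0.06 − 1.96×0.02153)/0.02132 = 0.835, so power is 0.80

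| q in both arms | Observed rates, control vs intervention | Ratio | Power |
|---|---|---|---|
| 0% | 2% vs 8% | 4.0 | 0.80 |
| 3% | 5% vs 11% | 2.2 | 0.61 |
| 6% | 8% vs 14% | 1.75 | 0.49 |

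For a smaller true excess, 2% vs 5%, power is 0.38, 0.23 and 0.18 in the same three rows.

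**6. Unequal non-medical departures.** Take a true medical excess of 3 points in the intervention arm (2% vs 5%).
- 1.5 points more non-medical departures in controls: observed difference 3 − 1.5 = 1.5 points.
- 3 points more in controls: 3 − 3 = 0.
- 5 points more in controls: 3 − 5 = −2, a reversed sign.
- 3 points more in the intervention arm: 3 + 3 = 6, an overstated harm.

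The bias can go either way, and the documents do not say which way, if any.

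**The case against.** **A stronger reading is tempting.** A reader might infer that the measure is biased against the control arm and so hides exercise-related events, because only the standard program runs longer than usual and patients know their arm. One could assume that 5% of controls (about 10 of 205) leave in the added week, with medical terminations of 2% (4) in controls and 5% (10) in the intervention arm. The count would then read 4 + 10 = 14 versus 10, in favour of the intervention.

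The documents do not support this:
- Both arms are planned for four weeks, and the Study setting section describes three- to four-week programs as the usual range.
- Patients consent before allocation.
- No departure rates are given, and nothing says that controls leave early or that a three-week stay is coded as premature termination.
- A more demanding program could equally lose more patients in the intervention arm.
- The reversal comes entirely from assuming no non-medical departures in the intervention arm. With 5% in both arms the counts are 14 versus 20, and the direction is preserved.

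**Other fair objections.** The list does hold the end date and diagnoses, so the timing of a departure is known and some causes might be inferred. The Harms section sets no threshold or safety conclusion. Controls also exercise, and severe heart failure is excluded, so no excess risk is shown. With few events, even a clean comparison has little power: 4 versus 10 of 205 gives a Fisher p of 0.17.

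**What stands.** These objections remove the claim of a control-arm bias. They leave the narrower point intact: an end date is not a reason, a diagnosis at discharge is not linked to the termination, and mixing causes weakens a medical signal even when the arms do not differ in non-medical departures. Nor is this detail left to another document: the Harms section names the measures, and the article says that it contains the original study protocol.

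**Conclusion.** The point holds in a limited form. As written, the harm comparison cannot tell a medically caused termination from a personal departure, and it does not capture acute hospital transfers during the stay. Under assumed rates of 2% versus 8%, equal non-medical departures of 3% or 6% reduce power from 0.80 to 0.61 or 0.49 and the ratio from 4.0 to 2.2 or 1.75. A differential bias is possible in this open-label trial, in either direction, but is not shown. The longer control stay is one conceivable reason, no more. The sizes rest wholly on assumed rates; the structural defect does not. This is a cheap improvement that bears on what the trial may say about safety. It does not affect the primary outcome.

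**What to change.** **Record.** In the pseudonymized list described under Confidentiality, add (a) a reason code for each early termination: acute transfer, cardiac event, death, other medical, non-medical; and (b) a field for any acute hospital transfer during the stay, whether or not it ended the program. Complete both in the same way in each arm. Recruitment is ongoing, so complete them from centre records for patients already enrolled, where available, and before the identifying study list is destroyed.

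**Report.** In the Harms section, state that medically caused termination, acute transfer and death are reported by arm, separately from non-medical departures. Add inpatient treatment after discharge by arm from the resource-use item already collected, noting that it depends on the 12-month response (assumed 70%).

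**Cost.** Two extra columns, a little data entry and one more table. Reasons may be incomplete for patients already treated. If the change counts as a substantial modification, it goes to the ethics committee and the register as the Trial design section sets out. No visits or treatment procedures change.

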### Ancillary and post-trial care

Ancillary and post-trial care are not planned. Compensation for harms due to study participation is also not planned.

### Participant timeline

Table 3 shows the full schedule of recruitment, interventions, and assessments.

**Table 3 Tab3:** Schedule of enrollment, intervention, and assessments

*Activity*	*Responsibility*	*Duration*	*P*	*T0*	*T1*	*T2*	*T3*
**Recruitment**							
Written information	Rehabilitation center	10 min	x				
Information by telephone	Rehabilitation center	10 min	x				
Randomization	Rehabilitation center, principal investigator	5 min	x				
**Intervention**							
Rehabilitation	Rehabilitation center	4 weeks		x	x		
**Assessments**							
Clinical examination	Rehabilitation center	45 min		x	x		
Documentation of treatment	Rehabilitation center	15 min			x		
Questionnaire	Principal investigator	30 min		x	x	x	x

*P* Preparation, *T0* Beginning of the rehabilitation, *T1* End of the rehabilitation, *T2* 3-month follow-up, *T3* 12-month follow-up

### Sample size

As a minimum important difference for the 12-month follow-up, we defined 0.2 points of the total cardiac anxiety score (0 to 4 points [15, 16]). Although 0.2 points represent only 5% of the scale range, we consider this small gain to be relevant because we are comparing two comprehensive rehabilitation programs. Assuming a standard deviation of 0.6 points [43], 0.2 points correspond to a standardized mean difference of 0.33. To detect this difference with a two-sided error of 5% and a power of 80%, 286 participants are required. Further assuming a response rate of 70% in the 12-month follow-up, we plan to recruit 410 participants (intervention group: n = 205; control group: n = 205) to be able to detect the minimal important difference also in a complete-case analysis. For our primary intention-to-treat analysis with multiple imputation of missing follow-up scores, a difference of 0.2 points is detected with a power of about 92%.

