### Allocation

Randomization is performed in a one-to-one ratio. The randomization sequence was generated by the principal investigator (MB) using Stata 16.0. Blocks of different size were combined randomly. Allocation concealment is ensured by sealed, opaque, and consecutively numbered envelopes. The envelopes are opened in the study center for randomization only after participants have given informed consent. The group assignment is documented in the study center in the study list through the identification number.

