### Statistical methods

We will analyze short-term (end of rehabilitation and 3-month follow-up) and long-term effects (12-month follow-up) using different models and publish the findings separately. We will use mixed models if more than one measurement point needs to be considered, i.e., end of rehabilitation and 3-month follow-up, and generalized linear models otherwise. If baseline scores are available, these will be included as a covariate when estimating the treatment effect. If outcomes are binary, a logit link will be used. High depression, high generalized anxiety, and high cardiac anxiety, as well as age, sex, and education, are tested as possible moderators of the treatment effect on our primary outcome cardiac anxiety assessed at the 12-month follow-up.

For health economic evaluation, we will calculate an incremental cost-effectiveness ratio [44]. Assessments of costs employ a societal perspective [41, 45]. Effectiveness is measured using quality-adjusted life years as derived from the 12-month assessment of the EQ-5D-5 L [28, 30]. The incremental cost-effectiveness ratio is calculated by dividing the difference in costs between both interventions by the difference in effectiveness between both interventions. Bootstrapping is used to compute a 95% confidence interval of the incremental cost-effectiveness [44].

Missing data will be imputed using chained equations [46]. We will create 20 independent data sets with complete values. Parameter estimates of the models will be combined in accordance with Rubin’s rules [47]. Statistical tests will be regarded as significant if the two-sided p-value of a test is less than 0.05. An up-to-date version of Stata (StataCorp, College Station, Texas, USA) will be used to conduct the analyses.

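### The stated 92% power of the primary multiple-imputation analysis is the unadjusted power with all 410 outcomes observed; the stated inputs support about 80%

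*Protocol article*

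**What the plan says.** The Sample size section sets the target difference: "As a minimum important difference for the 12-month follow-up, we defined 0.2 points of the total cardiac anxiety score". It scales it: "Assuming a standard deviation of 0.6 points [43], 0.2 points correspond to a standardized mean difference of 0.33". It then gives the number of analysable patients: "To detect this difference with a two-sided error of 5% and a power of 80%, 286 participants are required". It allows for non-response: "Further assuming a response rate of 70% in the 12-month follow-up, we plan to recruit 410 participants" ("intervention group: n = 205; control group: n = 205"), so that the target difference stays detectable in complete cases. The closing sentence turns to the primary intention-to-treat analysis and says that with "multiple imputation of missing follow-up scores, a difference of 0.2 points is detected with a power of about 92" per cent.

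The Statistical methods section plans chained equations with 20 completed data sets and says: "Parameter estimates of the models will be combined in accordance with Rubin’s rules". It also plans to use the baseline score as a covariate where one exists. Table 2 lists the cardiac anxiety total at T0, T1, T2 and T3. Neither section gives a correlation between baseline and 12-month scores, an R² for the imputation model, or a fraction of missing information.

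**The concern.** The section gives two powers for the same difference, SD, significance level and 410 recruits: 80% for complete cases and about 92% for multiple imputation. Imputation is the only stated difference between them, so the text credits it with the whole gain. Filling in a missing outcome adds no observation, and Rubin's rules add a between-imputation variance for that reason.

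At stake is the stated power of the primary analysis of the primary outcome. The sentence implies a type II error of about 8% at the minimum important difference, whereas the stated inputs imply about 20%. The Discussion says the results will inform pension insurers about implementation across Germany, so readers may well refer to the planned power if the result is null.

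**Working it through.** **Inputs.** From Sample size: difference 0.2, SD 0.6, two-sided 5%, 205 per arm, 70% response. From Allocation: "Randomization is performed in a one-to-one ratio". From Statistical methods: m = 20 imputations and Rubin's rules. The correlations and R² values in steps 4 to 6 are assumptions, because the article gives none.

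**1. The plan's own sample size.** d = 0.2/0.6 = 0.333. The noncentral t gives 143 per arm for 80% power, or 286 in total, as stated. Then 286/0.7 = 408.6, so 409; the plan takes 410. Both steps are correct.

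**2. Where 92% comes from.** Power = Φ(0.2/SE − 1.96), with SE = 0.6·√(2/n).
- n = 205 observed per arm: SE = 0.0593, 0.2/SE = 3.375, power 92.1% (noncentral t 92.0%). This is the stated figure.
- n = 0.7 × 205 = 143.5 per arm: SE = 0.0708, 0.2/SE = 2.824, power 80.6% (noncentral t 80.3%).

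The stated value matches 410 observed outcomes. The plan expects 0.7 × 410 = 287, leaving 123 to impute.

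**3. What Rubin's rules give without predictors.** Total variance T = W + (1 + 1/m)·B.
- W = 2 × 0.36/205 = 0.003512 (all 410 scores treated as known).
- W + B = 2 × 0.36/143.5 = 0.005017 (information in the 287 observed scores), so B = 0.001505.
- With m = 20, T = 0.003512 + 1.05 × 0.001505 = 0.005092, SE = 0.0714, power 80.0%.

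Using 92% amounts to setting B to zero. A simulation of 3,000 trials (30% missing, m = 20, no predictive auxiliaries) gave 91.8% with full data, 79.5% for complete cases and 79.0% for multiple imputation.

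**4. Informative auxiliaries, no baseline covariate.** The variance is (2 × 0.36/205)·[R² + (1 − R²)/0.7].

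| Assumed R² | Power |
|---|---|
| 0 | 80.6% |
| 0.25 | 83.5% |
| 0.50 | 86.5% |
| 0.80 | 90.0% |
| 1 | 92.1% |

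**5. Baseline adjustment, 30% missing.** The variance is multiplied by (1 − r²).

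| Assumed r | Power, 287 observed | Power, 410 observed |
|---|---|---|
| 0.3 | 84.1% | 94.3% |
| 0.4 | 86.9% | 95.7% |
| 0.5 | 90.3% | 97.4% |
| 0.55 | 92.2% | 98.1% |
| 0.6 | 94.2% | 98.8% |

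The middle column is the complete-case power and, to a close approximation, the imputation power with the same covariate. Simulated baseline-adjusted imputation (1,500 trials per value, Monte Carlo standard error about 1 point) gave 77%, 82%, 90% and 93% at r = 0, 0.3, 0.5 and 0.6.

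**6. Both together.** The variance is (2 × 0.36·(1 − r²)/205)·[q + (1 − q)/0.7], where q is the share of the remaining variance explained by T1/T2. With r = 0.5 and q = 0.2 it is 0.003512 × 0.75 × 1.343 = 0.003537, which gives a power of 92.0%.

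**The case against.** The best defence is that the planned analysis is not the unadjusted comparison behind the 80%. Baseline cardiac anxiety will be a covariate, and the T1 and T2 scores can enter the imputation model. With r of about 0.55, or r = 0.5 and modest help from T1/T2, the primary analysis would reach about 92% despite 30% non-response. This part stands. A reader might infer that the design cannot have 92% power, or that it could only if missing scores were predicted perfectly. The article does not support either inference: the second holds only without the baseline covariate, and the first would need a correlation that the article does not give.

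The defence does not rescue the sentence, however. No correlation is stated, and the text does not rest the 92% on adjustment. Baseline adjustment would lift complete-case power about equally, so it cannot explain 80% against 92%. If the SD of 0.6 were already a residual SD, power would stay near 80%. The agreement of 92% with the unadjusted full-data value points to how it was obtained, although the article does not show the calculation.

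A second defence is that the 92% did not set the sample size and that a finished trial is read from its estimate and confidence interval, which under Rubin's rules would carry the missing-data uncertainty. That also stands. It limits the consequence but does not make the stated power correct.

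**Conclusion.** The figure is wrong as written. About 92% is the unadjusted power with every one of the 410 outcomes observed. On the section's own inputs (difference 0.2, SD 0.6, 70% response, no covariate information) the imputation analysis has about 80%, so type II error is about 20% instead of 8%. The 80% takes the scores as missing completely at random and the imputation model as having no useful predictors. Under the assumed correlations of 0.3 to 0.6, the planned adjusted analysis would have about 84% to 94%, so 92% is possible but unsupported.

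A reader might also infer that the trial is too small. It is not, by its own target: 286 analysable patients, inflated to 410, still give 80% power. The error lies in the claimed power of the primary analysis and leaves the sample size, the analysis and the data collection untouched.

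**What to change.** Replace the last sentence of the Sample size section with: *On these assumptions (SD 0.6, 70% response, no covariate adjustment) the primary multiple-imputation analysis has a power of about 80%.*

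If a higher figure is wanted, state the assumed baseline-to-12-month correlation, or the auxiliary R² of the imputation model, and calculate the power with 30% of outcomes missing. Show it as an assumption (for example about 90% at r = 0.5), say whether 0.6 is a total or a residual SD, and give the complete-case power on the same basis.

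The cost is one sentence, repeated wherever else the figure is reported, and a less favourable stated power. No extra patients and no change to the analysis are needed.
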